Enamel defects of higher prevalence have a significant impact on the oral health of affected children [1]. Understanding the current prevalence of early enamel wear in the primary dentition, caused by various etiologies such as abrasion, attrition, and acid erosion, or the combination of these factors, is crucial. Additionally, it is essential to investigate the synergistic effect of these factors on teeth with compromised mineral structure. This knowledge is of paramount importance for the development and direction of public health policies aimed at the prevention and appropriate treatment of these conditions, as well as the promotion of better oral health in the pediatric population. Currently, there is a gap in the literature regarding the precise quantification of the prevalence and the combined etiological factors contributing to early enamel wear in children, highlighting the need for comprehensive epidemiological studies to guide effective public health strategies.

The introduction of new concepts and indices is important for advancing the understanding and management of dental conditions. In this context, we present the Childhood Early Oral Aging Syndrome (CEOAS) and the associated index proposed for validation. This concept aims to unify the assessment of early enamel wear in the primary dentition by relying on observed signs and reported symptoms from patients, rather than focusing solely on isolated etiologies. The index seeks to integrate and evaluate various factors that may contribute to premature and non-physiological loss of dental structure, including both intact and hypomineralized enamel wear. The goal is to provide a more comprehensive and practical approach to diagnosing and treating early wear, considering the complex interaction of the involved factors. Thus, the proposed index may contribute to a more effective approach to identifying and managing early wear in children.

Therefore, the aim of the present study was the development and validation of a Childhood Early Oral Aging Syndrome index for the primary dentition as a diagnostic and epidemiological survey tool.

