### Content validation by specialists

**Creation of content validity form**

**Table pone.0310543.t003:** 

**Content validity of Childhood Early Oral Aging Syndrome (CEOAS) index.** Dear specialists, This index was developed to provide a reliable, standardized tool for the investigation of clinical signs and symptoms related to early oral aging in childhood, with the inclusion of enamel defects, which are currently highly prevalent. The main purpose of the index is to serve as a tool for epidemiological surveys and enable knowledge on the prevalence and severity of tooth wear in the pediatric population, contributing to the planning of health actions based on the data collected. We need your specialized opinion on the degree of relevance of each item to the domains measured. Your review should be based on the relevance, clarity and applicability of the score developed for the CEOAS index, as found in Table 3. We would be grateful for verbal or written suggestions that enable us to improve the content of the index.

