#### Selection of reviewers (specialists)

The selection of specialists for the assessment will be based on the individual experience of doctoral professors specializing in pediatric dentistry, who will be chosen to ensure content validity, following recommendations. Following recommendations for content validation, at least six specialists will be selected [6]. The recruitment period for specialists will take place between July 29, 2024, and September 16, 2024.

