**Items and assessment and validation criteria of the CEOAS index**				
Is the CEOAS index relevant to the diagnosis of early oral aging syndrome?	1	2	3	4
	It is not relevant.	Relevant, but needs major revision.	Relevant, but needs minor revision.	Very relevant
Is the CEOAS index clear for the diagnosis of early oral aging syndrome?	1	2	3	4
	It is not clear	Clear, but needs major revision.	Clear, but needs minor revision.	Very Clear
Is the CEOAS index relevant with regards to communication among health professionals and researchers?	1	2	3	4
	It is not relevant.	Relevant, but needs major revision.	Relevant, but needs minor revision.	Very relevant
Is the CEOAS index applicable for diagnoses and epidemiological surveys?	1	2	3	4
	It is not applicable.	Applicable, but needs major revision.	Applicable, but needs minor revision.	Very applicable

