#### Calculation of content validity index (CVI)

The CVI will be calculated on a scale level based on the universal agreement method (S-CVI/UA). The classification of relevance should be recoded as 1 (scale score of 3 or 4) or 0 (scale score of 1 or 2). The universal agreement (UA) score is given as 1 when the item achieves 100% agreement among the specialists (only scores 3 and 4 for all items). Otherwise, the UA score is given as 0. The S-CVI/UA is equal to the sum of the UA scores divided by the number of items.

Sum of UA scores

S-CVI/UA = ______________________

Number of items

CVI values higher than 0.83 will be considered acceptable [7].

After the validation of the index, an observational study will be conducted to identify the prevalence of early wear in the primary dentition using the Childhood Early Oral Aging Syndrome index (CEOAS), and to investigate possible associated etiological factors. The study report will adhere to the STROBE guidelines for cross-sectional studies.

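### Item 4 of Table 3 takes one applicability rating for two uses of the index, so a failing or loosely read score cannot be assigned to either use

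*Protocol article*

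**What the plan says.** The Introduction of the protocol article closes by describing an "index for the primary dentition as a diagnostic and epidemiological survey tool", which names two uses. The introductory text of the specialists' form (Creation of content validity form) ranks them: "The main purpose of the index is to serve as a tool for epidemiological surveys".

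Table 3 has four items, each rated 1 to 4:

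- Item 1, relevance: "Is the CEOAS index relevant to the diagnosis of early oral aging syndrome"
- Item 2, clarity: "Is the CEOAS index clear for the diagnosis of early oral aging syndrome"
- Item 3, relevance for communication between professionals and researchers
- Item 4, applicability: "Is the CEOAS index applicable for diagnoses and epidemiological surveys"

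Item 4 has one set of anchors for both uses. Its score of 2, for example, reads "Applicable, but needs major revision".

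Under Selection of reviewers, "at least six specialists will be selected". Under Calculation of content validity index (CVI), ratings of 3 or 4 become 1 and ratings of 1 or 2 become 0. An item earns a UA score of 1 only if all specialists agree. S-CVI/UA is the sum of UA scores over the number of items, and a value above 0.83 is acceptable. Review of items invites suggestions. Attributing a score to each item provides for a group meeting when a specialist gives a 1.

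**The concern.** Item 4 is double-barrelled. Its two halves are the two uses in the aim, and an informed specialist could judge them differently. By the article's own definitions, scores 2 and 3 rest on hypersensitivity, compromised function and pulp involvement. A specialist might find these workable in a clinic but not in a field survey. Another might find the scores adequate for counting severity in a population but too coarse for an individual child.

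Diagnosis is at least named in items 1 and 2, on relevance and clarity. Survey use appears only inside item 4. Yet the article plans a prevalence study with the index as the next step after validation, so survey use is the one that step relies on. At stake is whether the sponsor can say which use the panel endorsed and, if the index fails, which use needs revision.

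**Working it through.** The article states no CVI result, so there is no figure to reproduce. The check asks whether the planned score can tell different specialist opinions apart.

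**Inputs.** Four items (Table 3); at least six specialists (Selection of reviewers); recoding, unanimity rule, formula and threshold above 0.83 (Calculation of CVI).

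**Step 1: possible values.** S-CVI/UA = (sum of UA scores) / (number of items).

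- Four items, as written: 0, 0.25, 0.50, 0.75, 1.00. Only 1.00 exceeds 0.83.
- Five items, with item 4 split by use: 0, 0.2, 0.4, 0.6, 0.8, 1.0. Only 1.0 exceeds 0.83.

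In both cases acceptance requires every item to be unanimous.

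**Step 2: opinion patterns.** Assume that items 1 to 3 each have UA = 1, that five of six specialists find the index applicable for both uses, and that the sixth holds one of four opinions. On the strict reading the sixth gives 3 or 4 only if both uses are acceptable; on the loose reading, if at least one is. The joint form scores (3 + UA of item 4)/4. The split form scores (3 + UA for diagnosis + UA for surveys)/5.

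| Sixth specialist accepts | Joint, strict | Joint, loose | Split |
|---|---|---|---|
| both uses | 4/4 = 1.00 | 4/4 = 1.00 | 5/5 = 1.0 |
| diagnosis only | 3/4 = 0.75 | 4/4 = 1.00 | 4/5 = 0.8 |
| surveys only | 3/4 = 0.75 | 4/4 = 1.00 | 4/5 = 0.8 |
| neither | 3/4 = 0.75 | 3/4 = 0.75 | 3/5 = 0.6 |

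**Step 3: reading the table.** On the strict reading a pass means both uses, but the three failing patterns share the value 0.75. On the loose reading three patterns share the value 1.00, and in two of them one use was not endorsed. The split total is 0.8 for either single-use pattern, but the two item-level UA scores show which use fell short. A larger panel does not help, because the information is lost within each specialist's single rating.

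**Step 4: other routes to the information.** A score of 1 calls a meeting, which could bring out the use in question. A score of 2 also sets UA to 0 but calls no meeting. Only an optional, unscored comment could then show which use was meant.

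**The case against.** The strongest reply is that the item says what it means. It asks about both uses, so a specialist who accepts only one should not endorse it and can answer 1 or 2, which both recode to 0. A false pass would need every specialist with a doubt about one use to read the item loosely; one strict reader with such a doubt blocks acceptance. This stands. A reader might infer that a one-use specialist has no valid answer, or that the aim cannot be answered from these data. The documents support neither: a unanimous 3 or 4 under a strict reading covers both uses, and the aim does not promise a separate verdict for each.

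Three further points also stand:

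- Diagnosis has its own relevance and clarity items, so it does not rest on item 4 alone.
- Comments are invited, and the meeting after a score of 1 may resolve a failure. This takes the trigger to cover item 4, although its parenthesis mentions only relevance and clarity.
- It is tempting to say that the form's introduction will lead raters to answer for surveys alone. A main purpose does not exclude a second one, and nothing shows that raters would overlook the word for diagnosis in the item itself.

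Two gaps remain. The form does not state the strict reading, and a score of 2 fails the index with no planned step to learn why.

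**Conclusion.** The point holds as a weakness in item wording and attribution. It is not an error in the CVI arithmetic and does not invalidate the planned index. A pass supports both uses if all specialists read item 4 strictly; if some do not, it may hide a use that was not endorsed. A fail caused by a 2 on item 4 leaves S-CVI/UA at no more than 0.75 with the failing use unidentified, unless a comment happens to name it.

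Item 4 is one of four items, but that 25% share is only a count and not a measure of harm. If everyone reads strictly, splitting the item does not change the accept or reject decision and adds only attribution. The verdict assumes that specialists can hold different views of the two uses. The score definitions make this plausible, but the article does not show it. The change is a cheap improvement worth making.

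**What to change.** Replace item 4 with two items, each rated 1 to 4: (4a) applicability for diagnosis in the individual child, and (4b) applicability for epidemiological surveys. Report the UA score for each and claim only the use or uses that reach agreement.

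If the ratings have already been collected, put the two questions to the same panel, or report that applicability was rated jointly.

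The threshold of 0.83 needs no change, since with five items 0.8 still fails and only 1.0 passes. The cost is one more question on an online form and one more item on which the panel must be unanimous.

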#### Review of items

During the validation process, the specialists will be asked to critically review the content prior to assigning scores. Verbal or written suggests for improving the content will be encouraged.

#### Attributing a score to each item

After the review, the specialists will attribute a score to each item (Table 3) corresponding to their assessments in terms of the relevance, clarity and applicability of the content and send their assessments before the deadline stipulated for the process. To assess the content, if a specialist indicates "1" on Table 3 (Not relevant/Not clear), a discussion meeting will be held with the group of specialists. This meeting will address and clarify any doubts or issues raised, ensuring consensus and accuracy in the content evaluation.

#### Calculation of content validity index (CVI)

The CVI will be calculated on a scale level based on the universal agreement method (S-CVI/UA). The classification of relevance should be recoded as 1 (scale score of 3 or 4) or 0 (scale score of 1 or 2). The universal agreement (UA) score is given as 1 when the item achieves 100% agreement among the specialists (only scores 3 and 4 for all items). Otherwise, the UA score is given as 0. The S-CVI/UA is equal to the sum of the UA scores divided by the number of items.

Sum of UA scores

S-CVI/UA = ______________________

Number of items

CVI values higher than 0.83 will be considered acceptable [7].

After the validation of the index, an observational study will be conducted to identify the prevalence of early wear in the primary dentition using the Childhood Early Oral Aging Syndrome index (CEOAS), and to investigate possible associated etiological factors. The study report will adhere to the STROBE guidelines for cross-sectional studies.
